### CRDS Database (China)

In December 2018, the National Clinical Research Center for Kidney Disease, the Center for Chronic Non-communicable Disease Prevention and Chinese Center for Disease Control and Prevention jointly established the Chinese Renal Disease Data System (CRDS). By the end of

November 2022, the CRDS database contained 24 Grade 3A hospitals, including 16,953,679 patients with data collected from 1994 to 2022, and consisting mostly of hospital-wide data. Data governance has been completed in 19 hospitals with 15,245,055 patients. The data of rest 5 hospitals has been governed in the CRDS database after 2022 and given the characteristics and of the CRDS database, we will exclude hospitals with data only from nephrology departments; with 20 remaining hospitals that will be included. Observation start date will be January 1 2015 and observation end date will be 31 December 2020 according to quality and situation of CRDS database.

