### 3.3 Study Population

Patients  $\geq 18$  years old with two consecutive eGFR measurements indicating stage 3 CKD ( $\geq 30$  and  $< 60$  mL/min/1.73m^2 using CKD-EPI (preferred) or MDRD equation) recorded more than 90 days apart (max. 730 days), meeting the inclusion criteria will be included in the study and constitute the denominator for the calculation of the prevalence of undiagnosed stage 3 CKD. A subset of the study population will be identified with no encounters with a diagnosis code for CKD any time prior to the study index date (for primary objective 2). The observation period will vary based on the period of data coverage, which may be unique to each data source. In CRDS database observation start date will be January 1, 2015, and observation end date will be 31 December 2020.

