### **3.5 Participant Follow-up**

CKD diagnosis status will be assessed using data from the  $\geq 12$ -month baseline period until six months post-index for the calculation of undiagnosed CKD prevalence. To assess time to CKD diagnosis (primary objective 2), patients will be followed from the index date to the earliest of their follow-up end date (due to death or transfer out of database) or end of data coverage period

To assess CKD management and monitoring quality indicators (secondary objective 3), patients will be followed starting from the six months post index date until the follow-up end date (due to death or transfer out of the database) or end of data coverage, whichever comes first.

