### 1. Detection and recognition of CKD

- Patients receiving a UACR test within first 6 months of follow-up

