### 2. Monitoring of kidney function and complications

Patients receiving the following tests within first 18 months of follow-up

- Serum Cr test (outpatient)
- Patients receiving a UACR test (outpatient)
- Serum calcium
- Phosphate
- Albumin
- Bicarbonate
- Potassium
- Hemoglobin
- Albuminuria

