### 6. Management of BP

- Patients receiving BP measurement any time during follow-up
- At least one BP measurement within 6 months
- In patients with least one BP measurement within 6 months (starting 6 months post index), patients with at least one BP measurement  $\leq 140/90$  mm Hg in the first or second year of follow-up
- In patients with least one BP measurement within 6 months (starting 6 months post index), patients with at least one systolic BP measurement  $< 120$  mm Hg in the first or second year of follow-up

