The proportion of patients achieving each of the quality indicators will be calculated for diagnosed and undiagnosed CKD patients. Estimates will be stratified by patient subgroups (section 4.4). Estimates will be calculated separately for all patients as well as the subset with complete follow-up data during the specified interval over which the quality measure is to be assessed (for data sources with information on enrollment).

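### The all-patients quality-indicator proportions are pulled down by the 31 December 2020 data end, and the two BP target items rise with the number of readings

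*Protocol*

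**What the plan says.** For secondary objective 3, section 3.5 says that "patients will be followed starting from the six months post index date until the follow-up end date", which is death, transfer out or the end of data coverage. For CRDS, section 3.2 fixes the coverage: "Observation start date will be January 1 2015 and observation end date will be 31 December 2020". Section 3.4 asks for 12 months in the database before the first qualifying eGFR but for no minimum time after index.

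The windows in section 4.2 differ by indicator:

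- Domain 1: "Patients receiving a UACR test within first 6 months of follow-up".
- Domain 2: "Patients receiving the following tests within first 18 months of follow-up".
- Domain 3: one year for statins and for ACE inhibitors or ARBs; no window for the SGLT2 items.
- Domain 6: one item counts a BP measurement at any time in follow-up. Two target items look at the first or second year.
- Domain 7: HbA1c testing in the first and second year.

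Each BP target item is limited to patients with a reading in the first six months of indicator follow-up. It then counts "patients with at least one BP measurement" on target.

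Section 5.2 reports simple proportions for diagnosed and undiagnosed patients, once for everyone and once for "as well as the subset with complete follow-up data during the specified interval over which the quality measure is to be assessed". The second version is conditional on the data source having enrolment information.

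**The concern.** There are two separate problems.

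**Calendar truncation.** A patient indexed late in the data has a window that runs partly or wholly past the data end. If that patient stays in the all-patients denominator, an event after the cut-off cannot be seen, so the patient can only lower the proportion. Longer windows suffer more, so indicators with different windows are not comparable either. Secondary objective 3 reports attainment by diagnosis status, and a reader would take a low figure as a gap in care when part of it is missing observation time.

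**Number of readings.** A target item met by any single on-target reading gives a frequently measured patient more chances to pass. Two groups with the same BP distribution but different numbers of readings would show different proportions. Complete follow-up does not remove this.

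**Working it through.** **Inputs from the protocol.** Data end 31 December 2020 (sections 3.2 and 3.3). Indicator follow-up opens at index + 6 months (3.5). Windows of 6, 12, 18 and 24 months from that opening (4.2), taking the one-year medication window to start there too. About 27,000 eligible CRDS patients (5.5). The protocol gives no figure for truncation or BP readings, so there is nothing of its own to reproduce here.

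**Assumptions.** Index dates are spread evenly over M months to the data end. M = 57 if the 12-month look-back falls inside the observation period (index from April 2016). M = 69 if the look-back may precede January 2015 (index from April 2015).

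**Step 1: incomplete windows.** A window of W months is complete only if index is at least 6 + W months before the data end. The incomplete share is (6 + W)/M.

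| Window W | M = 57 | M = 69 |
|---|---|---|
| 6 months | 12/57 = 21.1% | 12/69 = 17.4% |
| 12 months | 18/57 = 31.6% | 18/69 = 26.1% |
| 18 months | 24/57 = 42.1% | 24/69 = 34.8% |
| 24 months | 30/57 = 52.6% | 30/69 = 43.5% |

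The share with no indicator follow-up at all (index after 30 June 2020) is 6/57 = 10.5% or 6/69 = 8.7%.

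**Step 2: effect on the level.** Suppose 50% truly attain an indicator, with attainment spread evenly over the window (both assumed). Patients with a partial window contribute half on average, so the all-patients proportion is 0.5 × (M − 6 − W/2)/M.

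- 6 months: 0.5 × 48/57 = 42.1%; 0.5 × 60/69 = 43.5%
- 12 months: 0.5 × 45/57 = 39.5%; 0.5 × 57/69 = 41.3%
- 18 months: 0.5 × 42/57 = 36.8%; 0.5 × 54/69 = 39.1%
- 24 months: 0.5 × 39/57 = 34.2%; 0.5 × 51/69 = 37.0%

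**Step 3: effect on the group difference.** Diagnosis status uses codes up to six months after index. A patient indexed after June 2020 has less than that to receive a code, so is more likely to be classed undiagnosed, and has no indicator follow-up. Let a be the proportion coded by index and b the further proportion coded evenly over the next six months. Keep true attainment at 50% in both groups, and let q = 0.5 × (M − 6 − W/2)/(M − 6).

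- Diagnosed: q × (M − 6)(a + b) / [(M − 6)(a + b) + 6(a + b/2)]
- Undiagnosed: q × (M − 6)(1 − a − b) / [(M − 6)(1 − a − b) + 6(1 − a − b/2)]

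With M = 57, W = 6, a = 0.10 and b = 0.20, q = 0.5 × 48/51 = 0.4706. The diagnosed group reads 0.4706 × 15.3/16.5 = 43.6% and the undiagnosed group 0.4706 × 35.7/40.5 = 41.5%, a gap of about 2.2 points. Over a from 0.10 to 0.30, b from 0.10 to 0.20, both values of M and all four windows, the gap is about 0.7 to 2.2 points.

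**Step 4: BP target items.** Assume systolic BP only, mean 145, between-patient SD 14 and within-patient SD 10 mm Hg. The chance of at least one of k readings at or below 140 is the average of 1 − [1 − Φ((140 − m)/10)]^k over patient means m ~ N(145, 14²).

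| Readings k | At least one ≤ 140 |
|---|---|
| 1 | 38.6% |
| 2 | 51.5% |
| 4 | 63.1% |
| 8 | 72.7% |

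The last reading alone gives about 38.6% whatever k is. Everyone in this calculation has at least one reading, in line with the item's qualifying condition.

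**The case against.** **The remedy is already planned.** The same sentence provides a complete-follow-up estimate, so it would be wrong to say that late-index patients count as failures throughout. This stands. A reader might infer that CRDS, as hospital data, cannot produce that estimate. The protocol does not say so. Its own counts lean the other way: relaxing inclusion criterion 2 to a single visit (sensitivity analysis 3) raises the eligible number from about 27,000 to about 46,000, which suggests that some presence rule was applied in CRDS. That rule concerns time before index, however, so it does not show that post-index completeness can be determined. What remains open is whether the subset applies to CRDS and which estimate leads.

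**Denominator details may belong in the SAP.** In part. But the protocol already fixes the all-patients version as a simple proportion, with no censoring.

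**More testing is the care difference.** For indicators that count tests or measurements performed, more testing of diagnosed patients is what the indicator is meant to show. This stands. A reader might infer that all the indicators favour diagnosed patients without any difference in care. The readings argument supports that only for the two BP target items, and the protocol does not show that diagnosed patients are measured more often.

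**BP items have a qualifying reading.** Patients with no indicator follow-up are therefore not failures there. This stands; it does not alter the dependence on number of readings. The indicators after starting a drug likewise appear limited to initiators.

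**Incomplete windows in both groups do not bias the comparison.** Largely right. Step 3 shows that the differential part is small.

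**Conclusion.** The point holds in limited form. As planned, the all-patients proportions understate attainment, and more so for longer windows: about 17-21% of patients have an incomplete 6-month window, 26-32% a one-year, 35-42% an 18-month and 43-53% a two-year window. An assumed true 50% would read about 34-44%. These figures rest on even index dates. The late-index distortion of the diagnosed-versus-undiagnosed comparison is about 1-2 points on assumed coding rates, so a large bias between groups from this source is not supported.

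The two BP target items depend on measurement frequency by construction. How much that matters between groups cannot be sized from the protocol, and the BP figures above are illustrative only.

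This concerns one descriptive secondary objective, but the correction is cheap and worth making before analysis.

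**What to change.** 1. State that the complete-window estimate is the main one for CRDS. Where enrolment data are absent, define completeness by calendar: index by 31 December 2019, 30 June 2019, 31 December 2018 or 30 June 2018 for 6-, 12-, 18- and 24-month windows. Handle death and transfer out by censoring, since a calendar rule alone ignores them.
2. Alternatively, report cumulative incidence with censoring. Use this in any case for the BP item counted at any time in follow-up, which has no fixed window. Section 5.2 already censors time to diagnosis.
3. Keep the all-patients proportion as a secondary figure, with the share of incomplete windows beside it, by group.
4. Report the two BP target items also on the last or mean reading in each year, with the number of readings by group. Keep the existing version for comparison with other countries.

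The cost is wording, some programming and smaller denominators. With even index dates, the longest window keeps 27,000 × 27/57 ≈ 12,800 patients (about 15,300 with M = 69), before restrictions such as diabetes for HbA1c or a qualifying BP reading.

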## **5.3 Bias**

### **5.3.1 Methods to Minimize Bias**

The identification of patients with undiagnosed vs. diagnosed CKD relies on laboratory eGFR results, and the assumption that the absence of a CKD diagnosis code (e.g., ICD 9/10)

indicates that the patient is yet to be diagnosed with the condition by the physician. As this information is being inferred from EMR records, our assumptions may result in the misclassification of patients. The accuracy of our algorithm to identify patients with undiagnosed CKD is unknown. However, bias due to misclassification should be minimized, as our definition of CKD using eGFR results is based on an established clinical definition. Additionally, for patients identified as “undiagnosed”, we will also examine whether therapies for CKD (e.g., ACEi, ARB) are administered in the 12 month period following the index date (2nd eGFR result between 30-<60) to understand the likelihood that the patient is actually undiagnosed e.g., a code for CKD does not appear in their medical records but they are receiving treatment for CKD.

### **5.3.2 Adjustment for Multiple Comparisons**

Not applicable.

### **5.3.3 Study Limitations**

Although large retrospective databases can be used to identify and track cohorts of patients representing real-world populations, the results of this study should be considered in the context of the biases that are inherent to this type of design.

This study is subject to the following limitations:

- Data collected in a real-world setting may lack information on specific covariates and laboratory investigations. We will, however, assess the level of covariate missingness. The potential impact of missingness on the outcome of interest will be investigated.
- Coding may be a limitation itself due to sensitivity and specificity, and caution is required when interpreting any clinical associations.
- The analysis will examine the proportion of undiagnosed CKD among those who are tested/screened for CKD only; this could have the effect of biasing the proportion of undiagnosed versus screening all individuals for CKD.
- There is a risk of misclassification (diagnosed vs. undiagnosed) if CKD diagnosis is made in clinical settings that do not contribute data to the selected database.
- The generalizability of the results of this study may not be applicable to CKD patients who differ from the study population or countries not included in the analysis.
- There may be unmeasured confounding that may have an impact on risk estimates and may differ between countries and settings

## **5.4 Interim Analyses (Optional)**

Not applicable.

## **5.5 Sample Size and Power Calculations**

If the prevalence of undiagnosed CKD is between 60% and 80%, then a sample size of 1,000 patients will be sufficient to estimate the prevalence rate with a margin of error of  $\pm 3\%$  in a 95% CI per institution/country (6% width of 95% CI).

According to phase I of REVEAL-CKD in China: in the feasibility assessment report the Prevalence and consequences of undiagnosed chronic kidney disease in China, the number of patients who met the inclusion and exclusion criteria in the Chinese Renal Disease Data System (CRDS) database is about 27,000 and the number of patients who met the inclusion and exclusion criteria of sensitivity analysis in the CRDS database is about 46,000^3.

## **6. STUDY CONDUCT AND REGULATORY DETAILS**

### **6.1 Study Conduct**

The study proposal will be reviewed by the Evidence Review Team (ERT) for approval. Upon approval, a statistical analysis plan (SAP) will be created to outline the statistical procedure/table shells etc. Relevant approvals will be obtained for data use where necessary (e.g. local ethics approval). Results will be presented as abstracts and manuscripts.

#### **6.1.1 Procedures**

Not applicable (no primary data collection).

#### **6.1.2 Quality Control**

Data management and analyses will be performed by a local vendor in China. Quality control of programming will be performed via double-checks of programming codes by an independent programmer.

The extent of missing data will be investigated, and concerns for bias resulting from missing data will be addressed (e.g., via sensitivity analyses), as deemed appropriate based on the variable.

### **6.2 Protection of Human Subjects**

The observational study will be performed in accordance with ethical principles that are consistent with the Declaration of Helsinki, International Conference on Harmonisation (ICH) Good Clinical Practices (GCPs), Guidelines for Good Pharmacoepidemiology Practices (GPP), and the applicable legislation on Non-Interventional Studies and/or Observational Studies.

The Investigator will perform the observational study in accordance with the regulations and guidelines governing medical practice and ethics in the country of the observational study and in accordance with currently acceptable techniques and know-how.

#### **6.2.1 Subject Informed Consent (Primary Data Collection Only)**

Not applicable (no primary data collection).

#### **6.2.2 Confidentiality of Study/Subject Data (Primary Data Collection Only)**

This study does not involve any primary data collection. Data will be extracted from existing databases and stored in accordance with local regulations for data protection, to protect patient confidentiality. Results will be presented on an aggregate level, ensuring that no individual can be identified.

### **6.3 Collection and Reporting of Adverse Events/Adverse Drug Reactions**

As this study is solely based on secondary data (no primary data collection will be performed), there is no requirement for adverse events to be recorded nor reported.

## 8. APPENDICES

**Table A1. ICD-9/10 diagnosis coding definitions for identifying CKD**

| Description                                 | ICD-9                   | ICD-10                         | ICD-10CN2016#                                                                                                                                                                                                                   |
|---------------------------------------------|-------------------------|--------------------------------|---------------------------------------------------------------------------------------------------------------------------------------------------------------------------------------------------------------------------------|
| Primary Study Definition             |                         |                                |                                                                                                                                                                                                                                 |
| Chronic kidney disease, Stage (I)           | 585.1                   | N18, N18.1                     | N18, N18.801                                                                                                                                                                                                                    |
| Chronic kidney disease, Stage (II)          | 585.2                   | N18.2                          | N18.802                                                                                                                                                                                                                         |
| Chronic kidney disease, Stage (III)         | 585.3                   | N18.3, N18.30, N18.31, N18.32  | N18.803                                                                                                                                                                                                                         |
| Chronic kidney disease, Stage (IV) (severe) | 585.4                   | N18.4                          | N18.804                                                                                                                                                                                                                         |
| Chronic kidney disease, Stage V             | 585.5                   | N18.5                          | N18.001, N18.002(D63.8*)                                                                                                                                                                                                        |
| End stage renal disease                     | 585.6                   | N18.6                          | N18.0, N18.805(J99.8*), N18.806(G94.8*), N18.807(G63.8*), N18.808(I32.8*), N18.809(I43.8*), N19.x01                                                                                                                             |
| Chronic kidney disease, unspecified         | 585.9                   | N18.9                          | N18.9                                                                                                                                                                                                                           |
| Hypertensive CKD                            | 403.x, 404.x            | I12.x, I13.x                   | I12, I13                                                                                                                                                                                                                        |
| Diabetes with renal manifestation           | 250.4x                  | E10.2.x, E11.2x, E13.2x, E14.2 | E10.2, E11.2, E12.2, E13.2, E14.2,                                                                                                                                                                                              |
| Disorders from impaired renal function      | 588.x                   | N25                            | N25                                                                                                                                                                                                                             |
| Sensitivity Analyses #1              |                         |                                |                                                                                                                                                                                                                                 |
| Chronic kidney disease, Stage (III)         | 585.3                   | N18.3, N18.30, N18.31, N18.32  | N18.803                                                                                                                                                                                                                         |
| Chronic kidney disease, Stage (IV) (severe) | 585.4                   | N18.4                          | N18.804                                                                                                                                                                                                                         |
| Chronic kidney disease, Stage V             | 585.5                   | N18.5                          | N18.001, N18.002(D63.8*)                                                                                                                                                                                                        |
| End stage renal disease                     | 585.6                   | N18.6                          | N18.000, N18.805(J99.8*), N18.806(G94.8*), N18.807(G63.8*), N18.808(I32.8*), N18.809(I43.8*), N19.x01                                                                                                                           |
| Sensitivity Analyses #2*             |                         |                                |                                                                                                                                                                                                                                 |
| Chronic renal insufficiency                 | 582, 583, 585, 586, 587 | N03, N05, N18, N19, N26.9      | N03, N03.0, N03.1, N03.2, N03.3, N03.4, N03.5, N03.6, N03.7, N03.8, N03.9, N05, N05.0, N05.1, N05.2, N05.3, N05.4, N05.5, N05.6, N05.7, N05.8, N05.9, N18, N18.801, N18.802, N18.803, N18.804, N18.001, N18.002(D63.8*), N18.0, |

| Description | ICD-9 | ICD-10 | ICD-10CN2016#                                       |
|-------------|-------|--------|-----------------------------------------------------|
|             |       |        | N18.9, N19, N26.x01, N26.x02, N26.x00, N11.8, N11.9 |

| Sensitivity Analyses #2 (continued) |                                                                                  |                                                                                                                                                                                                                                          |                                                                                                                                                                                                                                                                                                                                                                                                                            |
|-------------------------------------|----------------------------------------------------------------------------------|------------------------------------------------------------------------------------------------------------------------------------------------------------------------------------------------------------------------------------------|----------------------------------------------------------------------------------------------------------------------------------------------------------------------------------------------------------------------------------------------------------------------------------------------------------------------------------------------------------------------------------------------------------------------------|
| Hypertensive nephropathy            | 403.xx, 404.xx                                                                   | I12, I13                                                                                                                                                                                                                                 | I12, I13                                                                                                                                                                                                                                                                                                                                                                                                                   |
| Acute renal failure                 | 572.4, 580.xx, 584.xx, 580.0, 580.4, 580.89, 580.9, 582.4, 791.2, 791.3          | K76.7, N00.3, N01.3, N08, N00.8, N00.9, N17, N03.8, R82.3, R82.1                                                                                                                                                                         | K76.7, N00.3, N00.8, N00.9, N01.3, N03.8, N17, N17.0, N17.1, N17.2, N17.8, N17.9, R82.1, R82.3, N10.x00, N10.x01                                                                                                                                                                                                                                                                                                           |
| Miscellaneous                       | 274.10, 440.1, 442.1, 453.3, 581.xx, 593.xx, 753.0, 753.3, 866.00, 866.01, 866.1 | M10.3, I70.1, I72.2, I82.3, N04, N02.2, N08, N28.81, N28.83, N28.1, N13.5, N13.8, N13.4, N13.7, N28.80, N28.89, N28.82, N28.9, R80.2, Q60.2, Q60.5, Q63.0-Q63.8, S37.009, S37.019, S37.029, S37.039, S37.049, S37.059, S37.069, S31.001, | I70.1, I72.2, I82.3, M10.3, N02.2, N04, N04.0, N04.1, N04.2, N04.3, N04.4, N04.5, N04.6, N04.7, N04.8, N04.9, N08*, N13.4, N13.5, N13.7, N13.700, N13.701, N13.8, N28.1, N28.8, N28.807, N28.821, N28.812, N28.800, N28.9, Q60.2, Q60.5, Q63, Q63.0, Q63.1, Q63.2, Q63.3, Q63.8, Q63.9, R80, S31.0, S31.000, S37.0, S37.000, S37.001, S37.002, S37.003, S37.004, S37.010, S37.011, N07, N06, N12, N14, N15, N16*, Q61, N25 |

\* Adapted from Winkelmayr et al. (2005)

